#### Secondary efficacy assessments

The statistical description and inference of the secondary indicators will be based on the characteristics of the data, and the appropriate descriptive indicators and hypothesis testing methods will be selected.

The comparison of general conditions between the two groups will be analysed by appropriate methods according to the type of indicators. The comparison between the groups of measurement data will be compared by the *t* test (homogeneity of variance, normal distribution) or the Wilcoxon rank sum test according to the distribution of data, and the chi-square test or exact probability method (if the chi-square test is not applicable) will be used for count data. The Wilcoxon rank sum test or stratified chi-square test (CMH test) will used for ranked data. Data analyses will be performed by statisticians who are independent of the study team and who are blinded to the group assignments. The acceptable significance level for all analyses will be *P* < 0.05.

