#### Sample size

This study is a randomised controlled trial to evaluate modified ultrasound scalpel haemorrhoidectomy versus the Milligan-Morgan operation for mixed haemorrhoids. According to previous studies [19], the mean value of the experimental group is 10.50, the mean value of the control group is 13.40, and the standard deviation is 3.46 and 3.66, respectively. Two-sided tests is needed, with a test level of 0.05. Using the PASS 15.0 software, the sample size of the two groups is 33, and according to the 15% loss of follow-up, 78 subjects will be expected to be finally collected.

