#### Statistical analysis

This study is a randomised, single-blind, parallel controlled study. The primary endpoints are the time to incision healing and the time to return to normal activities after modified ultrasonic scalpel haemorrhoidectomy. It can be considered that the recovery time after the treatment of modified ultrasonic scalpel haemorrhoidectomy is approximately normally distributed when testing the superiority hypothesis of modified ultrasonic scalpel haemorrhoidectomy and conventional haemorrhoidectomy. The hypothesis of superiority will be tested in a one-tailed approach, with a *P* value of 0.025 or less considered to indicate statistical significance.

All analyses will be performed with R 4.3.2.

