#### Primary efficacy assessments

The primary efficacy measures in this trial are the time to postoperative wound healing and the time to return to normal activity. An equivalence test will be used, and the test hypothesis is as follows:

H0: the recovery time of the intervention group-the recovery time of the control group is ≤ 0;Hα: the recovery time of the intervention group-the recovery time of the control group is > 0.

The recovery time of the two groups will be calculated, and the 95% confidence interval (CI) of the difference between the two groups will be determined. The difference from baseline between the trial group and the control group can be approximated as following a normal distribution, and thus the efficacy analysis will be analysed with the use of T. The superiority hypothesis will be tested between the modified ultrasonic scalpel haemorrhoidectomy group and the conventional haemorrhoidectomy group, and the test *α* = 0.025 (one-sided test). If the *p* value is less than or equal to 0.025, the superiority of postoperative recovery time of the modified ultrasonic scalpel haemorrhoidectomy group compared with the conventional haemorrhoidectomy group will be verified.

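### A blanket P < 0.05 for all analyses conflicts, read literally, with the one-sided 0.025 rule set for the primary superiority test

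*Protocol article*

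**What the plan says.** Four places in the protocol article bear on the level of the primary test.

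- Sample size: "Two-sided tests is needed, with a test level of 0.05".
- Statistical analysis: "The hypothesis of superiority will be tested in a one-tailed approach, with a *P* value of 0.025 or less considered to indicate statistical significance".
- Primary efficacy assessments: the same one-sided 0.025 level is repeated, with the decision rule that opens "If the *p* value is less than or equal to 0.025, the superiority of postoperative recovery time". The section also says that "the 95% confidence interval (CI) of the difference between the two groups will be determined". It labels the test an equivalence test and writes the alternative hypothesis as recovery time in the intervention group minus that in the control group being greater than zero.
- Secondary efficacy assessments, last sentence: "The acceptable significance level for all analyses will be *P* < 0.05".

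**The concern.** The primary p value is defined as one-tailed and is to be compared with 0.025. The closing sentence on secondary assessments covers every analysis, states no sidedness and makes no exception for the primary endpoints. If it is applied to the one-tailed primary p, the bar drops from 0.025 to 0.05. A result with a one-sided p of, say, 0.03 would then be a failure under one sentence of the protocol and a success under another. At stake is the verdict on a borderline result, and a false-positive rate for superiority that doubles on each primary endpoint. A threshold that can be chosen after the p value is known is not prespecified.

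**Working it through.** **Inputs (Sample size section).** "the mean value of the experimental group is 10.50, the mean value of the control group is 13.40"; "the standard deviation is 3.46 and 3.66, respectively"; 33 per group before losses; 15% loss; 78 in total. Allocation is 1:1 (Randomisation and blinding). Power is not stated.

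**Step 1: reproduce the plan's figure.**
- Difference: 13.40 − 10.50 = 2.90.
- Common SD: √[(3.46² + 3.66²)/2] = √[(11.972 + 13.396)/2] = √12.684 = 3.561.
- Normal approximation, n per arm = 2·SD²·(z₁₋α + z_power)²/difference², with one-sided α = 0.025 and 90% power: 2 × 12.684 × (1.960 + 1.282)²/2.90² ≈ 31.7, so 32.
- Exact noncentral t: 32 per arm gives 89.4% power and 33 per arm gives 90.3%, so 33 is the smallest n that reaches 90%. At 80% power the t calculation gives 25. The stated 33 therefore points to 90% power.
- Losses: 33/0.85 = 38.8, so 39 per arm and 78 in total. The plan's figures are reproduced.

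**Step 2: compare the levels.**

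| Rule | Critical z | n per arm for 90% power (t) | Power at 33 per arm |
|---|---|---|---|
| Two-sided 0.05 (Sample size) | 1.960 | 33 | 90.3% |
| One-sided 0.025 (Statistical analysis; Primary efficacy assessments) | 1.960 | 33 | 90.3% |
| One-sided p against 0.05 (closing sentence, read literally) | 1.645 | 27 | 94.8% |

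The first two rows are the same rule in the favourable direction. Only the third differs. It would need 27/0.85 = 31.8, so 32 per arm and 64 in total, which is not what the protocol states.

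**Step 3: which results are affected.**
- A one-sided p of 0.03 is a two-sided p of 0.06; 0.04 is 0.08. Both fail the first two rules and pass the third.
- Standard error of the difference with 33 per arm: 3.561 × √(2/33) = 0.877.
- Smallest significant difference, 64 degrees of freedom: 1.669 × 0.877 = 1.46 at one-sided 0.05; 1.998 × 0.877 = 1.75 at one-sided 0.025.
- Observed differences between about 1.46 and 1.75 change verdict. If the planned 2.90 is true, the chance of landing in that band is 94.8% − 90.3% = 4.5 percentage points. If there is no difference, it is 0.05 − 0.025 = 2.5 points.

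**The case against.** The strongest reply is that the specific rule governs the general one. The one-sided 0.025 rule is stated twice for the primary test and is matched by a 95% confidence interval. The P < 0.05 sentence closes a section on secondary outcomes, after a list of tests for secondary and baseline data. Read as a conventional two-sided level, it agrees with everything else. This largely stands: it is the more natural reading, and it keeps the point small. It does not remove the point, because the sentence says all analyses, and the sentence just before it, on blinded independent statisticians, is not confined to secondary outcomes either.

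Three stronger readings are tempting, and the text does not support them.

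- That the sample-size section sets a different threshold. It does not: two-sided 0.05 and one-sided 0.025 share cut-off, n and power in the favourable direction.
- That a two-sided p might be held against 0.025, giving a stricter test. No section does this; each mention of 0.025 for the primary test is tied to a one-sided test.
- That the one-tailed test cannot declare the modified operation slower. As written, the alternative hypothesis (intervention minus control above zero) points only towards slower recovery. In addition, the planned 95% interval would show an unfavourable difference.

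**Conclusion.** The conflict is real but narrow. It lies between the closing sentence of Secondary efficacy assessments and the one-sided 0.025 rule of the two preceding analysis sections, and it arises only if that sentence is taken at its word. On that reading the one-sided type I error is 0.05 instead of 0.025 for each primary endpoint, and observed differences of about 1.46 to 1.75 change verdict. The protocol's own sample size shows that 0.025 one-sided was intended.

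This rests on the following assumptions: a t test with 33 evaluable patients per arm and the sample-size SDs; 90% power, inferred because none is stated; and a one-sided test that points towards shorter recovery, which the written alternative hypothesis contradicts. The band is in the units of the sample-size section, which does not say which of the two primary endpoints its means describe, so it should not be attached to either. The error rates are per endpoint and say nothing about the two endpoints jointly.

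**What to change.** 1. In Secondary efficacy assessments, replace the closing sentence with one that sets a two-sided level of 0.05 for secondary analyses only.
2. State one primary rule in the same words under Sample size, Statistical analysis and Primary efficacy assessments: two-sided 0.05 (equivalently one-sided 0.025 towards shorter recovery), reported with the 95% confidence interval, and superiority claimed only if the interval excludes zero in favour of the modified operation.
3. In Primary efficacy assessments, correct the hypotheses so that the alternative is a shorter time with the modified operation, and remove the equivalence label.

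The cost is wording in four sections. The 33 per arm, the total of 78 and the 90.3% power at 33 per arm stay as they are. The change should be made before any comparative results are seen.

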#### Methods in analysis to handle protocol non-adherence and any statistical methods to handle missing data

Data will be analysed on the basis of the full analysis set (FAS), per-protocol set, and safety set. FAS analysis is a fundamental principle of intention-to-treat and will include all patients enrolled in this trial. Analyses will be performed according to the intention-to-treat principle, with patients assessed according to the group to which they were randomly assigned, regardless of actual use or algorithm adherence. The per-protocol analysis is a subset of the FAS analysis, which will include only patients who fully complete the trial. Safety set analysis refers to the set of patients who will be treated and evaluated for safety. Multiple imputation will be used to address missing values based on appropriate exploration of missing mechanisms and in accordance with good practice.

#### Plans to give access to the full protocol, participant-level data, and statistical code

The datasets analysed during the current study and statistical code are available from the corresponding author on reasonable request, as is the full protocol.

### Oversight and monitoring

#### Audits

The ethics committee will locally monitor the quality of the trial after the first batch of patients is registered. The trial management team will meet every 3 months to check the implementation of the study, including the recruitment rates, data quality, and adverse event reporting.

#### Plans for communicating important protocol amendments to relevant parties

The protocol, statistical analysis plan, data safety management plan, informed consent, and recruitment materials were reviewed and approved by the Biomedical Research Ethics Committee of West China Hospital of Sichuan University. Any subsequent modifications will be submitted for review, and annual safety and progress reports will be submitted. In addition, the online trial registration form will be updated accordingly.

#### Availability of data and materials

The final trial data for this protocol can be supplied on request.

#### Communication plan

The research results will be disseminated through peer-reviewed publications and speeches at industry academic conferences.

## Discussion

There are many surgical methods for haemorrhoids, but each has its own advantages and disadvantages. Therefore, it is particularly necessary to explore a surgical method that not only does not damage anal sphincter function but can also restore the normal shape of the anus.

The choice of surgical instruments for mixed haemorrhoids should not only take into account the different symptoms and morphological characteristics of patients with mixed haemorrhoid lesions but also local related haemodynamic changes, microcirculation control disorders, and haemorheological pathophysiological changes; the concept of “minimally invasive” should be used as much as possible to achieve a good therapeutic effect and protect the fine functions of the anus, such as defecation control. The metal head of the ultrasonic scalpel is sharp and conducive to fine anatomy and is of great value in the operation of mixed haemorrhoids. Ultrasonic scalpel haemorrhoidectomy was reported to be applied in the clinic by Jane [22] and other investigators in 2001, and research has shown that ultrasonic scalpel haemorrhoidectomy can reduce the pain and postoperative bleeding of patients. Mushaya [23] et al. conducted a meta-analysis of the comparison between ultrasonic haemorrhoidectomy and traditional haemorrhoidectomy, and the results showed that the ultrasonic scalpel group had lower pain scores, a lower complication rate, and a faster recovery than the traditional surgery group. Research by Ravi Kumar [24] et al. showed that compared with the Milligan-Morgan operation, ultrasonic haemorrhoidectomy resulted in less blood loss (19.4 and 6.1 ml, respectively). Compared with the Milligan-Morgan method group, the ultrasonic scalpel group had lower VAS pain scores on the first day and the first and the second week after the operation. There were more complications, such as postoperative bleeding and urinary retention, in the Milligan-Morgan group. In a case study of 25 patients (ultrasound scalpel group) conducted by Tariq Ahmed Mala [25], the average operation time was 17.68 ± 2.84 min, and the average operation time of the control group was 28.44 ± 3.69 min. The average blood loss of the ultrasonic scalpel group and the control group was 8.96 ± 2.15 ml and 31.72 ± 3.28 ml, respectively. VAS pain scores on the first day after surgery were 5.92 ± 0.70 in the ultrasonic scalpel group and 8.52 ± 0.84 in the control group. The ultrasound scalpel group had a lower analgesic dose, engaged in walking earlier and returned to normal work faster. In previous research reports, the vast majority of ultrasonic scalpel haemorrhoidectomy procedures were open operations only using an ultrasonic scalpel to remove the haemorrhoids; the wound was left open and drained and healed naturally. Only two studies mentioned that the incision was closed [22, 26]. Another study showed that closing the incision is not beneficial; it is not conducive to drainage of the incision and may actually slow the healing process [27]. Before the start of this study, we conducted a preliminary study: 12 patients with mixed haemorrhoids were treated with open ultrasonic scalpel resection. Unfortunately, 8 of the 12 patients had blood in the stool 5–16 days after the operation, mainly the dripping of blood and jet-like bleeding, and the amount of bleeding was ≥ 5 ml each time. Among them, 4 patients had postoperative bleeding > 50 ml. All 4 patients underwent a second haemostatic operation under anaesthesia. During the operation, the wounds were found to have ulcers and erosions and extensive bleeding after ultrasonic scalpel resection. Upon inquiry into their medical history, the 8 patients with bleeding were found to have no primary underlying diseases (hypertension, heart disease, blood system diseases, etc.) and no history of long-term anticoagulant drug use. The reasons may be as follows: if only the ultrasonic scalpel is used to remove the haemorrhoids without suturing the incision, normal defecation activity after the operation will increase the abdominal pressure and anal pressure, which will increase the tissue tension in the anal area. Under repeated stimulation from stool, the coagulated tissues will easily crack and bleed, causing incision infection and delayed healing. Therefore, we modified the open ultrasonic scalpel haemorrhoidectomy procedure. While removing the internal haemorrhoid mucosa, we sutured the base of the incision with a figure of eight and designed this research plan to evaluate its clinical efficacy and safety.

A limitation of this study is that only the patients will be single-blinded; the researchers and patients cannot be blinded at the same time, which may impose a certain bias on the results. In addition, the sample size of this study will be small, and the findings will only represent the results of this clinical trial. The sample size needs to be further expanded in later stages to improve the level of evidence. Despite its limitations, we hope this trial will help provide a more optimised surgical approach in the selection of haemorrhoid surgery.

## Trial status

Participants are still being recruited. Enrolment began in July 2021, and the trial is expected to be completed by July 2023. Approximately two thirds of the recruitment is currently completed.

## Abbreviations

PPH: PROXIMATE® PPH haemorrhoidal circular stapler haemorrhoidopexy
RPH: Automatic haemorrhoid ligation
FEH: Ferguson’s with electrosurgical haemorrhoidectomy
AEs: Adverse events
SAEs: Serious adverse events
VAS: Visual analogue score
SF-36: 36-Item Short Form Health Survey
CCF-FI: Cleveland Clinic Florida Fecal Incontinence Score
CRF: Case report form
